### 3.3.1 Rationale for Test Product Dosage

In a Phase I study (P7081-5101), the maximum antiviral activity of RO5024048 in combination with Pegasys/Copegus for 28 days was observed following administration of 1000 mg BID. There was no increase in antiviral effect or additive benefit seen with the higher dose of 1500 mg BID (see Figure 1). In combination with Pegasys/Copegus in treatment-naïve patients, a high on-treatment virologic response with 1000 mg BID was observed and was independent of IL28B genotype in Study NV22621 (Pockros et al. 2011). Therefore, a dose higher than 1000 mg BID would not be expected to provide any additional antiviral activity. In Study NV20536, RO5024048 1000 mg BID administered in combination with Pegasys/Copegus for 12 weeks was associated with higher levels of on-treatment viral suppression and a greater decrease in HCV RNA during the first 12 weeks of treatment than were observed with RO5024048 500 mg BID, particularly in non-CC genotype 1 patients (Jensen et al. 2010). Therefore, the 1000-mg dose was chosen because of the high prevalence of the unfavorable IL28B genotype in the target population.

**Figure 1 Exposure–Response Curve for RO4995855 (Ctrough): Study 7081-5101**

[figure not shown]

Ctrough = minimum observed drug concentration during a dosing interval;  
HCV RNA = hepatitis C virus RNA.

The selected boceprevir dose in this study (800 mg thrice daily [TID]) is the currently approved dose for the treatment of CHC genotype 1 patients.

The doses selected for Pegasys/Copegus are based on currently approved doses for the treatment of CHC genotype 1 patients.

In Phase III studies of boceprevir, boceprevir was given for a maximum of 48 weeks. The preliminary results from Phase II studies of RO5024048 (NV20536 and NV22621) support RO5024048 treatment for up to 24 weeks. This study will examine if 24 weeks of RO5024048 and boceprevir is sufficient to achieve SVR when used in a QUAD regimen. The Pegasys/Copegus approved duration for the treatment of CHC genotype 1 patients is 48 weeks. This study will examine if a shorter duration of Pegasys/Copegus is sufficient to achieve SVR when used in a QUAD regimen. Therefore, in this study, boceprevir will be given for 24 or 48 weeks, RO5024048 will be given for 24 weeks, and Pegasys/Copegus will be given for 24 or 48 weeks.

### **3.3.2      Rationale for Patient Population**

The patient population of genotype 1 previous null responders to PEG-IFN/RBV therapy was chosen because it has the highest unmet medical need with the potential to benefit from treatment with a QUAD regimen of two DAAs in combination with Pegasys/Copegus.

### **3.3.3      Rationale for Biomarker Assessments**

Hepatitis C virus genotype 1 patients with different alleles (CC, CT, or TT) at one single nucleotide polymorphism (SNP) location (rs12979860) positioned upstream of the IL28B gene respond differently to PEG-IFN and RBV treatment, with CC being the best responder (Ge et al. 2009; Thompson et al. 2010). Although the C allele frequency of rs12979860 SNP varies from approximately 20% to more than 90% in population genetic sampling across the world (Khakoo et al. 2009), it is expected that the treatment-failure patient population will be enriched for patients with TT and CT genotype. Stratification of patients based on IL28B-related SNP will be required for balancing treatment arms for new investigative medicine trials involving PEG-IFN and/or RBV. Stratification based on IL28B-related SNP may help to assess the effect of IL28 genotype on treatment with DAAs.

Interferon gamma-induced protein 10kDa $\alpha$  is a baseline predictor (independent of IL28B) of IFN response. Plasma levels of IP-10 can be considered a surrogate marker for hepatic IFN-stimulated gene levels during HCV infection because the bulk of IP-10 is being secreted by the liver. IP-10 levels decrease during IFN/RBV or DAA treatment. Exploratory measurement of baseline IP-10 could provide information on whether baseline IP-10 levels affect treatment response.

## **3.4            OUTCOME MEASURES**

### **3.4.1      Efficacy Outcome Measures**

#### **3.4.1.1    Primary Efficacy Outcome Measure**

The primary efficacy endpoint will be SVR-12 (actual) outcome with response defined as an unquantifiable (less than the LLOQ [ $< 25$  IU/mL]) serum HCV RNA 12 weeks after the actual end of treatment (a single last unquantifiable HCV RNA within 8–20 weeks after the last day of study drug administration).

### **3.4.1.2      Secondary Efficacy Outcome Measures**

For the following measures, which are HCV RNA response outcomes, response is defined as an unquantifiable (less than the LLOQ [ $< 25$  IU/mL]) serum HCV RNA:

- Hepatitis C virus RNA response outcome at clinic visits over time
- Sustained virologic response 24 weeks after treatment (SVR-24 actual) outcome, defined as the HCV RNA response outcome  $\geq 20$  weeks after the last day of study drug administration
- Sustained virologic response 4 weeks after treatment (SVR-4 actual) outcome, defined as the HCV RNA response outcome within 2–8 weeks after the last day of study drug administration
- Hepatitis C virus ( $\log_{10}$  IU/mL) change from baseline to Week 24
- Occurrence of documented DAA resistance

### **3.4.2      Safety Outcome Measures**

The safety outcome measures for this study are as follows:

- Incidence and severity of adverse events (AEs) and SAEs and reasons for the discontinuation of any study medication. The Division of AIDS Table for Grading the Severity of Adult and Pediatric Adverse Events (ACTG) guidelines will be used to grade AEs.
- Clinically significant changes in vital signs, laboratory tests, and ECG results from screening/baseline

### **3.4.3      Pharmacokinetic Outcome Measures**

- Trough concentrations for RO4995855, RO5012433, and boceprevir

### **3.4.4      Exploratory Outcome Measure**

The exploratory outcome measure for this study is as follows:

- Interferon gamma-induced protein 10kDa levels will be measured at baseline in all patients.

## **4. MATERIALS AND METHODS**

### **4.1 PATIENTS**

Patients enrolled using protocol version 4 will not be permitted to be re-randomized to this study and enrolled for a second course of treatment. Patients who have been enrolled prior to protocol version 4 and randomized to Group C will be offered mericitabine, in addition to the treatment they are receiving. Maximum treatment durations for each component of a patient's regimen will be as follows:

- Boceprevir: 24 weeks (Arm A) or 48 weeks (Arm B)
- RO5024048: 24 weeks maximum
- Pegasys/Copegus: 24 weeks (Arm A) or 48 weeks (Arm B)

#### **4.1.1 Inclusion Criteria**

Patients must meet the following criteria for study entry:

1. Male or female aged 18 years and older
2. Serologic evidence of CHC infection by an anti-HCV antibody (Ab) test (current or historical)
3. Evidence of CHC infection > 6 months duration
4. Serum HCV RNA quantifiable at  $\geq 50,000$  IU/mL as demonstrated by the Roche COBAS® TaqMan® HCV Test
5. Evidence of HCV genotype 1a or 1b infection by molecular assay
6. The following information related to the patient's response to the previous course of PEG-IFN/RBV therapy must be available in the medical records of the patient: (1) approved doses of prior PEG-IFN/RBV treatment and the start/end date of previous treatment with PEG-IFN/RBV, (2) documentation of previous dose modifications or interruptions (or lack thereof) to ensure documentation of previous compliance with therapy, (3) HCV RNA prior to the start of previous treatment and at 12 weeks after the start of treatment (window of Week 11 to Week 16) showing a null response, defined as a  $< 2 \log_{10}$  IU/mL decrease in viral titer after at least 12 weeks of treatment with PEG-IFN/RBV, (4) HCV assay used, and (5) limit of detection of the assay used.
7. Patients must have discontinued prior HCV treatment at least 12 weeks prior to enrollment (receipt of first dose) in this trial.
8. Chronic liver disease consistent with CHC infection as seen via biopsy, using the scoring methods in [Appendix B](#). Patients designated as not having cirrhosis or incomplete/transition to cirrhosis must have had a liver biopsy consistent with CHC within 24 calendar months of the first dose. For patients with cirrhosis or incomplete/transition to cirrhosis, there is no time frame for the biopsy. Fibroscan assessment is allowed in such patients but must be performed within 12 calendar months of the first dose. An elasticity score of  $\geq 12.5$  kPa will be used to designate incomplete/transition to cirrhosis or cirrhosis (i.e., 'cirrhotic'). If an elasticity score of

- $\geq 9.5$  kPa but  $< 12.5$  kPa is returned, the patient must receive a liver biopsy to determine whether his or her case is described as 'cirrhotic' or 'non-cirrhotic'.
9. Patients with cirrhosis or incomplete/transition to cirrhosis must have an abdominal ultrasound, computed tomography (CT) scan, or magnetic resonance imaging (MRI) scan without evidence of hepatocellular carcinoma (within 6 months prior to randomization), an endoscopy without evidence of bleeding gastroesophageal varices (within 2 years prior to randomization), and a serum alpha-fetoprotein (AFP)  $< 100$  ng/mL ( $< 100$  µg/L).
  10. Normal cardiac troponin I value at the screening visit ( $< 0.100$  ng/mL)
  11. Serum total bilirubin less than the upper limit of normal (ULN) at the screening visit, unless there is a documented history of Gilbert's syndrome
  12. Negative serum pregnancy test at screening (for females of childbearing potential). Negative urine pregnancy test documented within the 24-hour period prior to the first dose of study drugs confirmed by a negative serum pregnancy test collected within 24 hours prior to the first dose of study drug
  13. Female patients of childbearing potential must agree to use two forms of non-hormonal contraception (i.e., condom, cervical barrier, intrauterine device [IUD], spermicide, or sponge) during treatment and after the last dose of boceprevir, RO5024048, and Copegus (in accordance with the locally approved label for Copegus). All males with female partners of childbearing potential must use two forms of effective contraception (combined) during treatment and following the last dose of Copegus in accordance with the locally approved label for Copegus.
  14. Willingness to give written informed consent and willingness to participate in and comply with the study requirements

#### **4.1.2      Exclusion Criteria**

Patients who meet any of the following criteria will be excluded from study entry:

1. Infection with any HCV genotype other than genotype 1a or 1b
2. Body mass index  $< 18$  or  $\geq 36$
3. Positive test at screening for anti-hepatitis A virus (HAV) IgM Ab, hepatitis B surface antigen (HBsAg), or anti-HIV Ab
4. History of having received RO5024048/boceprevir or any cross-resistant DAA agent at any previous time or use of any other systemic antiviral therapy with established or perceived activity against HCV  $\leq 3$  months prior to the first dose of study drug
5. Herbal agents (e.g., milk thistle)  $\leq 1$  month prior to the first dose of study drug and throughout the duration of the study
6. History of having received any investigational drug  $\leq 3$  months prior to the first dose of study drug or the expectation that such drugs will be used during the study. Patients enrolled in this study cannot be simultaneously enrolled in another study for research, diagnostic, or treatment purposes.

7. History or other evidence of a medical condition associated with chronic liver disease other than HCV (e.g., hemochromatosis, autoimmune hepatitis, Wilson's disease, alpha-1 antitrypsin deficiency, alcoholic liver disease, and/or toxin exposure)
8. Females who are pregnant or breastfeeding
9. Males with female partners who are pregnant
10. Absolute neutrophil count (ANC)  $< 1.5 \times 10^3$  cells/ $\mu$ L ( $< 1.5 \times 10^9$  cells/L)
11. Platelet count  $< 90 \times 10^3$  cells/ $\mu$ L ( $< 90 \times 10^9$  cells/L)
12. Hemoglobin concentration  $< 12$  g/dL (120 g/L) in females or  $< 13$  g/dL (130 g/L) in males or a baseline increased risk for anemia (e.g., thalassemia, sickle cell anemia, spherocytosis, history of gastrointestinal bleeding) or in those for whom anemia would be medically problematic
13. The use of colony-stimulating factors such as granulocyte colony-stimulating factor (G-CSF), erythropoietin, blood transfusion, or other therapeutic agents to elevate hematology parameters to facilitate patient entry into the study within the last 6 months
14. Any patient with a history of severe psychiatric disease, including psychosis and/or depression, characterized by a suicide attempt, hospitalization for psychiatric disease, or a period of disability as a result of psychiatric disease who does not agree to have a psychiatric evaluation at screening and who does not agree to have continued monitoring by a mental health specialist at least every 4 weeks during the study
15. History of immunologically mediated disease (e.g., vasculitis, cryoglobulinemia, inflammatory bowel disease, idiopathic thrombocytopenic purpura, lupus erythematosus, autoimmune hemolytic anemia, scleroderma, severe psoriasis [defined as affecting  $> 10\%$  of the body, where the palm of one hand equals 1% or if the hands and feet are affected], rheumatoid arthritis requiring more than intermittent non-steroidal anti-inflammatory medications for management). Patients with a history of celiac disease may enroll in the study.
16. History or other evidence of decompensated liver disease. Coagulopathy, hyperbilirubinemia, hepatic encephalopathy, hypoalbuminemia, ascites, and bleeding from esophageal varices are conditions consistent with decompensated liver disease.
17. Serum creatinine  $> 1.5$  times the ULN
18. History of pre-existing renal disease. Patients with a history of nephrolithiasis will be allowed.
19. Estimated creatinine clearance (CRCL) of  $\leq 70$  mL/min ( $\leq 1.17$  mL/sec), calculated by the Cockcroft-Gault formula (see [Appendix C](#))
20. Type 1 or 2 diabetes with glycosylated hemoglobin (HbA1c) of  $\geq 8.5\%$  at the screening visit

21. History or other evidence of chronic pulmonary disease associated with functional limitation
22. History of severe cardiac disease (e.g., New York Heart Association Functional Class III or IV, myocardial infarction within 6 months, ventricular tachyarrhythmia requiring ongoing treatment, unstable angina, or other significant cardiovascular disease). Patients with stable cardiac disease (e.g., 6 months after bypass surgery, stent replacement, etc.) as confirmed by a cardiologist will be permitted. In addition, patients with documented or presumed coronary artery disease or cerebrovascular disease should not be enrolled if in the judgment of the investigator an acute decrease in Hgb by up to 4 g/dL would not be well tolerated.
23. Patients with higher potential of duration of ventricular depolarization and repolarization (corrected) (QTc) prolongation as defined by duration of ventricular depolarization and repolarization (QT) interval for heart rate using Fridericia's formula (QTcF) > 450 ms (average from multiple readings) or notable resting bradycardia < 50 beats/min or notable resting tachycardia > 100 beats/min or personal or family history of congenital long QT syndrome or sudden death
24. History of uncontrolled severe seizure disorder
25. History of any neoplastic disease within the last 5 years, with the exception of localized or in situ carcinoma of the skin (e.g., basal or squamous cell carcinoma)
26. History of any systemic antineoplastic or immunomodulatory treatment (including supraphysiologic doses of steroids and radiation)  $\leq$  6 months prior to the first dose of study drug or the expectation that such treatment will be needed at any time during the study
27. Poorly controlled thyroid dysfunction
28. History or other evidence of a clinically relevant ophthalmologic disorder due to diabetes mellitus or hypertension or history or other evidence of severe retinopathy (e.g., cytomegalovirus, macular degeneration)
29. History of major organ transplantation with an existing functional graft
30. History or other evidence of severe illness or any other conditions that would make the patient, in the opinion of the investigator, unsuitable for the study
31. Use of contraindicated concomitant medications that are highly dependent on CYP3A4/5 for clearance, and for which elevated plasma concentrations are associated with serious and/or life threatening events. Potent CYP3A4/5 inducers are also contraindicated (Vitreliis™ USPI 2011).
32. Evidence of excessive alcohol, drug, or substance abuse (excluding marijuana use) within 1 year of the first dose
33. History of allergy to RBV, pegylated IFNs, or other IFNs

## **4.2 METHOD OF TREATMENT ASSIGNMENT AND BLINDING**

Approximately 60 patients who qualify for the study will be enrolled. Patients will be randomized in a 1:1 ratio. Randomization will be centralized and stratified by HCV genotype (1a or 1b) and by IL28B genetic polymorphism (CC, CT, or TT).

The study is double-blind, and neither study staff, monitors or patients will know which treatment arm individuals have been randomized to.

The randomization list will not be provided to the study center and to the monitors. Patients who have previously been enrolled in Group C will be unblinded and offered mericitabine, in addition to the treatment they are receiving, for a maximum of 24 weeks.

An IMC and safety project team will be unblinded for routine aggregate safety reviews. For purposes of modeling and simulation, drug resistance monitoring, and PK analysis, select members will be unblinded. In order for the Sponsor to make recommendations or decisions regarding further development of the drug, selected members of the project team will have access to the blinding code for interim analyses.

In order to facilitate analysis of the biologic samples collected in this study, the treatment code will be released—according to procedures in place to ensure the integrity of the data—to the responsible analytical person when the samples have been received at the analytical site and are ready for assay. The result of the analysis must not be released with individual patient identification until the database is closed.

If unblinding is necessary for patient management (in the case of a SAE), the investigator will be able to break the treatment code by contacting the interactive voice response system (IVRS). Treatment codes should not be broken except in emergency situations. If the investigator wishes to know the identity of the study drug for any reason, he or she should contact the Medical Monitor directly. The investigator should document and provide an explanation for any premature unblinding (e.g., accidental unblinding, unblinding due to a SAE).

As per health authority reporting requirements, Roche will break the treatment code for all unexpected SAEs (see Section 5.7) that are considered by the investigator to be related to the study drug.

All other individuals directly involved in this study will remain blinded until all patients have completed all study assessments and the database is cleaned and closed.

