### **4.3.3            Investigational Medicinal Product Accountability**

All investigational medicinal products (IMPs) required for completion of this study (RO5024048, boceprevir, Pegasys, Copegus) will be provided by Roche.

The investigational site will acknowledge receipt of IMPs, using the IVRS to confirm the shipment condition and content. Any damaged shipments will be replaced.

IMPs will either be disposed of at the study site according to the study site's institutional standard operating procedure or returned to Roche with the appropriate documentation. The site's method of IMP destruction must be agreed upon by Roche. The site must obtain written authorization from Roche before any IMP is destroyed, and IMP destruction must be documented on the appropriate form.

Accurate records of all IMPs received at, dispensed from, returned to, and disposed of by the study site should be recorded on the Drug Inventory Log.

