#### **4.6.1.1 Discontinuation from Study Drug**

All study medications should be stopped for individual patients for any of the following reasons:

- Hepatitis C virus RNA titer > 100 IU/mL by Week 24
- Quantifiable HCV RNA at Week 24
- Hepatitis C virus RNA virologic breakthrough before the end of treatment with boceprevir and/or RO5024048/placebo and/or Pegasys/Copegus. Virologic breakthrough is defined as:

A sustained increase in HCV RNA of  $\geq 1 \log_{10}$  IU/mL ( $\geq 2$  consecutive measurements) while on boceprevir/RO5024048 compared with the on-treatment nadir (where the nadir is a  $\geq 1 \log_{10}$  IU/mL decrease from baseline after 2 weeks of treatment or  $\geq 2 \log_{10}$  IU/mL decrease from baseline after 4 weeks of treatment)

Confirmed quantifiable HCV RNA ( $\geq 25$  IU/mL by  $\geq 2$  consecutive measurements) in a patient who had been previously confirmed as having unquantifiable HCV RNA ( $< 25$  IU/mL by  $\geq 2$  consecutive measurements) before the end of treatment with boceprevir/RO5024048

Response ( $< 25$  IU/mL by  $\geq 2$  consecutive measurements) to boceprevir/RO5024048 treatment and subsequent quantifiable viral load ( $\geq 25$  IU/mL by  $\geq 2$  consecutive measurements) once boceprevir/RO5024048 treatment has been completed (but Pegasys/Copegus treatment continues)

- Hepatitis C virus partial response before the end of treatment with boceprevir/RO5024048/Pegasys/Copegus/placebo, defined as an initial HCV RNA decline ( $\geq 1 \log_{10}$  IU/mL decrease from baseline after 2 weeks of treatment or  $\geq 2 \log_{10}$  IU/mL decrease from baseline after 4 weeks of treatment) followed by stabilization ( $\geq 2$  consecutive measurements similar to those at nadir) while on boceprevir/RO5024048/Pegasys/Copegus/placebo treatment and/or a HCV RNA  $\geq 1000$  IU/mL by the end of boceprevir/RO5024048/Pegasys/Copegus/placebo treatment of at least 4 weeks in duration
- Any confirmed Grade 4 laboratory abnormality deemed clinically significant (based on the investigator's assessment)
- A positive troponin value ( $> 0.100$  ng/mL)

RO5024048 should be stopped for individual patients for any of the following reasons:

- A creatinine clearance decrease  $\geq 35\%$  from baseline or  $< 60$  mL/min ( $< 1.00$  mL/sec) confirmed by repeat test, preferably within 1 week

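### Section 4.2 promises a double-blind to database closure, but for patients who complete 24 weeks of treatment the arm is evident after Week 24, because Arm A stops all drugs, Arm B continues, and no masking supply is described

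*Protocol*

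**What the plan says.** - **Blinding.** The title, the synopsis and section 3.1 call the study double-blind. Section 4.2 says: "The study is double-blind, and neither study staff, monitors or patients will know which treatment arm individuals have been randomized to". It names exceptions: the Internal Monitoring Committee, the safety project team, selected sponsor members, the analyst of the biologic samples, former Group C patients and emergency code breaks. All other people directly involved "will remain blinded until all patients have completed all study assessments and the database is cleaned and closed".
- **Treatment by arm.** Section 4.1 sets the maximum durations: "Boceprevir: 24 weeks (Arm A) or 48 weeks (Arm B"), "Pegasys/Copegus: 24 weeks (Arm A) or 48 weeks (Arm B") and, for both arms, "RO5024048: 24 weeks maximum". Table 1 shows Arm A in treatment-free follow-up after Week 24 and Arm B on boceprevir and Pegasys/Copegus to Week 48.
- **Supply.** Section 4.3.3 says: "All investigational medicinal products (IMPs) required for completion of this study (RO5024048, boceprevir, Pegasys, Copegus) will be provided by Roche". Sections 4.3.1 and 4.3.2 describe the same four products and no dummy capsule, tablet or injection.
- **Placebo.** For this study, the word survives only in the stopping rules of section 4.6.1.1, for example "before the end of treatment with boceprevir and/or RO5024048/placebo and/or Pegasys/Copegus".
- **Use of the data.** Section 2.2 includes an objective to compare safety and tolerability between the groups. Section 6.5 summarises adverse events by group over treatment and treatment-free follow-up together.

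**The concern.** The only planned difference between the arms is what happens after Week 24, and section 3.3.1 makes that duration a study question. Up to Week 24, hiding the planned duration needs no placebo because the regimens are identical. After Week 24 one arm takes capsules three times a day, daily Copegus and a weekly injection, and the other takes nothing. A design property stated in the title and in section 4.2 is therefore absent in the period when the arms differ.

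At stake are the judgements made at the site. Adverse events are elicited by questioning (5.3.2), causality is assessed by the investigator (5.3.4), and the investigator may stop a drug or withdraw a patient (4.6.1). After Week 24 these are made with the arm known for patients who completed 24 weeks, and they feed the safety and tolerability comparison. A reader who relies on the label would give that comparison more protection from reporting bias than it has.

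**Working it through.** The point is one of consistency, so the check sets the sections side by side. The protocol's one precision figure is reproduced first, to show what is not affected.

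**1. Precision of the primary estimate (6.1).** The half-width of a 90% normal-approximation interval with n = 30 is 1.645 × √(p(1 − p)/30).
- p = 0.45 or 0.55: 14.9 percentage points.
- p = 0.50: 15.0 percentage points.

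The stated ±15% is reproduced, and blinding does not enter it.

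**2. What each arm takes (Table 1, 4.1, 4.3.2).**

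| Period | Arm A | Arm B | Distinguishable? |
|---|---|---|---|
| Weeks 0–24 | RO5024048, boceprevir, Pegasys, Copegus | the same four | no |
| Weeks 24–48 | no drug | boceprevir, Pegasys, Copegus | yes |
| Weeks 48–72 | study complete (24 + 24 = 48) | no drug (48 + 24 = 72) | already known |

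Treatment differs for 48 − 24 = 24 weeks.

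**3. Could anything listed mask Weeks 24–48?** The four products in 4.3.1 to 4.3.3 are all active. The RO5024048 placebo implied in 4.6.1.1 is not described as a product. It would not help in any case, because RO5024048 ends at Week 24 in both arms and the gap lies in boceprevir and Pegasys/Copegus.

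**4. Who sees it?**
- The patient records every dose in a diary (4.3.2).
- The site reconciles returned drug (4.3.2), and Appendix A marks dispensing after Week 24.
- Appendix A times follow-up visits from the last dose, so Arm A leaves the treatment-visit calendar.
- Monitors verify source data (7.3).

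**5. Which patients?** Under 4.6.1.1 all drugs stop in either arm for quantifiable HCV RNA at Week 24, for breakthrough, for partial response and for some safety findings. Follow-up is then the same in both arms. A patient who stops everything by Week 24 therefore does not show the arm through the schedule. The protocol gives no expected number. With an assumed fraction d, the number revealed is 60 × (1 − d):

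| d | 0% | 10% | 20% | 30% | 40% | 50% |
|---|---|---|---|---|---|---|
| Revealed of 60 | 60 | 54 | 48 | 42 | 36 | 30 |

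**6. Which data?**
- *Exposed:* adverse event reporting, causality, discontinuation and retention after Week 24.
- *Little exposed:* SVR-12, an HCV RNA assay result (4.5.1.1); study laboratory tests, which are measured centrally (4.5.1.3); and ECGs, which are read centrally (4.5.1.4) and, as Appendix A is printed, not scheduled after Week 24 except at premature withdrawal.
- *Indirect route to SVR-12:* it is timed from the actual end of treatment, so a discontinuation decided with the arm known could still touch it.

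**The case against.** The best case for leaving the text alone is that little depends on it. The primary objective is to estimate SVR-12 in each group, no hypothesis test is planned (6.4), the endpoint is a laboratory value, and drug identity is never hidden. Being on or off drug after Week 24 is inherent in comparing two durations. All of this stands. It limits the consequence to one descriptive secondary comparison, but it does not make the statement in 4.2 true.

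A reader might infer more than the documents support:

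- *That every patient's arm is known from Week 24.* Patients who stop all drugs by then do not reveal it through the schedule.
- *That everything collected afterwards is compromised, the primary endpoint included.* Assay results and central readings are little exposed, and treatment differs only in Weeks 24–48. Arm B's later follow-up adds no further treatment difference.
- *That concealment also fails before Week 24.* Section 4.2 withholds the randomization list from centres and monitors, and the regimens are identical, so concealment of duration to Week 24 is already provided for.
- *That the safety comparison will be reported as blinded.* No section says so; the risk comes from the label.
- *That the placebo wording points to a hidden masking supply.* None is described. The synopsis and sections 4.1 and 4.2 mention a former Group C whose patients were unblinded and offered mericitabine. The wording fits that group, but this is an inference.

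**Conclusion.** The point holds within these limits. Section 4.2 contradicts Table 1 and sections 4.1 and 4.3.1 to 4.3.3. For each patient who completes 24 weeks of treatment, the arm is evident to patient, site and monitor afterwards: between 60 and 30 of 60 patients if 0% to 50% stop all drugs by Week 24, a range that is assumed. The effect is mainly on investigator- and patient-dependent safety and discontinuation data. The ±15% precision is unchanged and SVR-12 is little affected. The conclusion rests on the four listed products being the whole supply, which is how section 4.3.3 reads. Blinding and supply are fixed in the protocol, so an analysis plan could not repair the statement.

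**What to change.** 1. In the title, synopsis, 3.1 and 4.2, state that the assigned duration is concealed until Week 24 and that patients, sites and monitors are unblinded afterwards. If a masking supply exists, describe it in 4.3 instead.
2. Qualify, rather than delete, the sentence in 4.2 on blinding to database closure. Limit it to those who can stay blind, such as central readers.
3. Reconcile the placebo wording in 4.6.1.1 with the product list, or remove it.
4. In 6.5, report adverse events and discontinuations arising after Week 24 as open-label. The section now pools treatment and follow-up, so this means one added split.
5. State that sites are not told the arm before the Week 24 assessments are done. The exact release time must be reconciled with the drug-supply schedule. Waiting for the Week 24 HCV RNA result, or for a confirmatory sample drawn within 2 weeks, could delay Arm B supply or take Arm A past the 24-week maximum in 4.1.

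The cost is amendment wording, one extra split in the safety tables and agreement on release timing. The downside is losing the double-blind label.
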